# GOVERNANCE AND SAFETY

**Adverse Reaction Management**

The post injection education sheet will advise participants of the usual post-injection responses and how to manage any adverse events. Response to adverse events will involve:

For urgent events, with signs and symptoms of anaphylaxis a standard procedure code blue will be called if the participant is in the hospital. Anaphylaxis is rare and usually occurs within the first 30 minutes post injection. Participants will remain in the department for at least 30 minutes post injection. If outside the hospital, emergency department attendance is recommended and this is stated on the post injection information sheet.

For non-urgent events, participants will be advised to contact us and seek GP consultation if required. They will be offered consultation with [name] (Supervising Orthopaedic Surgeon), who will assess and manage the situation with recording on the Adverse Incident Assessment Form.

**Adverse Reaction Reporting**

Participants will be instructed through their post injection information sheets to report any such concerns to the research team. Adverse events attributable to the trial are one of the secondary outcome measures, they will be monitored by project investigators and be communicated directly to the Gold Coast Health Service District Human Research Ethics committee and the data/safety monitoring committee. An adverse event reportable to the data safety monitoring committee will be defined as one that requires hospitalization or antibiotic treatment of confirmed or suspected infection.

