**Primary objectives**

To discover whether:

1. there is agreement between the physiotherapist and the surgeon regarding selection of shoulder patients appropriate for subacromial injection.
2. care (subacromial corticosteroid and local anaesthetic injection) delivered by the physiotherapist is no worse than the same type of care delivered by the orthoapaedic surgeon, with respect to safety, access, effectiveness and efficiency.

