*** primary outcome measure stage 1**

**^ primary outcome measure stage 2**

| **Category** | **Measure** | **From** | **Timing** |
| --- | --- | --- | --- |
| **Clinical and Demographic Characteristics** | Age, sex, employment status, hand dominance, uni or bilateral | Participant | Baseline |
| Imaging to date and key findings | Referral | Baseline |
| Duration of symptoms | Participant | Baseline |
| Past treatments and costs – physiotherapy, injection, surgery, other | Participant | Baseline |
| Medications | Participant | Baseline |
| **Baseline outcome measures** | Impact and costs questionnaire | Participant | Baseline |
| Work Productivity and Activity Impairment Questionnaire (WPAI) | Participant | Baseline |
| Work Limitations Questionnaire (WLQ) | Participant | Baseline |
| Shoulder Pain and Disability Index (SPADI) | Participant | Baseline |
| 10 cm VAS patient perception of pain over the past 3 days | Participant | Baseline |
| EuroQual-5D-5L | Participant | Baseline |
| **Stage 1** | | | |
| **Clinical agreement** | Are there any safety contraindications to injection? | Clinicians | At time of assessment |
| Are there any safety precautions regarding injection? | Clinicians | At time of assessment |
| *** Would you provide subacromial injection today?** | Clinicians | At time of assessment |
| Are there any other reasons to exclude this participant from stage 2 | Clinicians | At time of assessment |
| **Stage 2** | | | |
| **Safety** | Incidence of adverse events | Adverse event reporting mechanism | Collated throughout |
| **Access** | Current new appointment booking dates with Orthopaedics and OPSC | Research Assistant | At time of intervention |
| **Effectiveness** | **^Shoulder Pain and Disability Index (SPADI)** | Participant | 6 weeks  12 weeks |
| 10 cm VAS patient perception of pain over past 3 days | Participant | 6 weeks  12 weeks |
| Global Rating of Change Scale | Participant | 6 weeks  12 weeks |
| EuroQual-5D-5L | Participant | 6 weeks  12 weeks |
| Physiotherapy attendances post injection | eMR / Groupwise | 6 weeks  12 weeks |
| 10 cm VAS patient satisfaction with care | Participant | 12 weeks |
| **Economic** | Staff costs for each clinician | Standard pay scales | 6 weeks  12 weeks |
| Impact and costs questionnaire | Participant | Baseline |
| Work Productivity and Activity Impairment Questionnaire (WPAI) | Participant | Baseline |
| Work Limitations Questionnaire (WLQ) | Participant | Baseline |

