**Data Safety monitoring**

The biostatistician will monitor the progress of this project through interim statistical analyses, and a data/safety monitoring committee will review any adverse events associated with the project.

Stopping rules will be applied to the following situations:

• Treatments found to be convincingly different

• Treatments found to be convincingly not different

• Adverse events too prevalent

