**DECLARATION**

The Principle Investigator, who is also the Physiotherapist delivering the injections in this proposed study, is presently seconded to a Program Manager post, funded through Queensland Health, Allied Health Workforce Advice and Coordination Unit (AHWACU) “Models Of Care” project funding. This research forms part of the work within that Program. AHWACU has no direct influence over the conduct of the research or its findings.

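### The safety outcome is defined two ways, and nothing stated keeps an investigator who knows the arm from deciding which adverse events count

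*Protocol*

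**What the plan says.** The second primary objective asks whether the physiotherapist's care is no worse than the surgeon's "with respect to safety, access, effectiveness and efficiency". How adverse events are counted therefore bears on a primary question, although SPADI is the measure marked as primary for Stage 2.

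The outcome is described in two places:

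- The outcome table under Outcome measures lists "Incidence of adverse events", drawn from the adverse event reporting mechanism and collated throughout, with no condition on cause.
- Adverse Reaction Reporting states: "Adverse events attributable to the trial are one of the secondary outcome measures, they will be monitored by project investigators". The same sentence sends these events to the ethics committee and to the data/safety monitoring committee.

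On who is involved, the Declaration describes the principal investigator as the person "who is also the Physiotherapist delivering the injections in this proposed study". Adverse Reaction Management offers participants with non-urgent events a consultation with the supervising orthopaedic surgeon, "who will assess and manage the situation with recording on the Adverse Incident Assessment Form".

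On the committee's remit, Adverse Reaction Reporting says "An adverse event reportable to the data safety monitoring committee will be defined as one that requires hospitalization or antibiotic treatment", the antibiotics being for proven or presumed infection. Data Safety monitoring says "a data/safety monitoring committee will review any adverse events associated with the project", and lists an excess of adverse events among the grounds for stopping.

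**The concern.** The two descriptions are different endpoints. One counts every adverse event. The other counts those that pass a causal judgement, and in a comparison of two injectors such a judgement can be coloured by knowing who injected. The protocol names no judge of attribution, gives no criteria and states no masking for that step. The investigators who monitor events include one of the two people being compared.

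At stake is the credibility of a conclusion that care is no worse on safety. If the attributable count is used and the person judging knows the arm, the difference between arms partly reflects that person's expectations. The committee's conflicting remit adds a second problem: it is unclear whether the body that would apply the adverse event stopping rule sees every event or only the most serious category.

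**Working it through.** **1. The plan's own figure.** The protocol gives no number for the safety comparison. Its only Stage 2 sample size is for SPADI non-inferiority (Sample size paragraph): margin 15, SD 21.7, α 0.05 with sidedness not stated, power 80%.

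- Normal approximation, one-sided 0.05: n per arm = 2 × 21.7² × (1.645 + 0.842)² / 15² ≈ 25.9, so 26.
- Noncentral t, one-sided 0.05: 27 per arm (power 0.806), which is the protocol's figure of 54 in total.
- Dropout: 54 / (1 − 0.15) = 63.5, so 64, or 32 per arm.

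The sample size reproduces. It matters here only because it sets the denominator for the safety comparison.

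**2. Outcome definition, side by side.**

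| Place | What is counted | Condition |
| --- | --- | --- |
| Outcome table | Incidence of adverse events | None |
| Adverse Reaction Reporting | Adverse events | Attributable to the trial |

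The table cites the reporting mechanism as its source. It can therefore be read alone, so that all events count, or through the reporting section, so that only attributable events count. The text does not say which governs.

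**3. Who could make the attribution call knowing the arm.**

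- *Injecting clinicians.* The Blinding section masks them only to each other's assessment findings. Each knows whom they injected, and one of them is the principal investigator.
- *Supervising orthopaedic surgeon.* No masking is stated, and the text does not say whether this is also the injecting surgeon.
- *Access to the injector's identity.* The treatment form is scanned into the clinical record. The physiotherapist treating after injection is asked not to look up who injected. No such request covers whoever assesses adverse events.

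The possible judges come from both professions, so no direction of bias can be assumed.

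**4. Sensitivity to a few calls.** Take the arm's rate as participants with a counted event divided by participants in the arm, and suppose a participant's only event is reclassified.

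- 32 per arm: 1/32 = 3.1 percentage points.
- 27 per arm: 1/27 = 3.7 percentage points.
- Two participants reclassified in one arm of 32: 2/32 = 6.25 percentage points.

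As a measure of how sparse the data are, an arm of 32 with no counted events has an exact one-sided 95% upper limit of 1 − 0.05^(1/32) = 8.9%.

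**5. Committee remit, side by side.** Adverse Reaction Reporting first says events are communicated to the committee, then limits reportable events to hospitalisation or antibiotic-treated infection. Data Safety monitoring sets no such threshold. Even if its reference to association with the project is read as a causal qualifier, lesser events would fall within one description and outside the other. The stopping ground for too many adverse events would be fed by different counts under the two.

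**The case against.** The strongest reply is that a reader might infer more than the protocol says.

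- *That only attributable events count.* This holds for the reporting section but not for the outcome table, which has no such filter. What stands is a contradiction, not a settled restriction.
- *That the injecting physiotherapist decides attribution, so the comparison favours that arm.* No section says so. The protocol has investigators monitor events; it does not assign them the causal judgement. The one named assessor of non-urgent events is an orthopaedic surgeon, from the comparator's profession.
- *That most events escape independent review.* The reporting section also sends events to the ethics committee and sets no severity threshold there, although as worded these are the attributable events. Data Safety monitoring has the committee review events broadly.

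Reporting also starts with participants who are not told the clinician's profession. That protects what is reported, but not a later judgement about cause. Finally, attribution criteria and analysis detail could properly sit in a statistical analysis plan or on the assessment form. That is fair for the detail. It does not dispose of two conflicts within the protocol over which events are the outcome and which reach the committee. An analysis plan cannot recover events that were never recorded or forwarded.

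**Conclusion.** The point holds as a conflict of definitions with an unprotected judgement attached. The safety outcome differs between the outcome table and the reporting section, nothing stated prevents an involved person who knows the arm from deciding attribution, and two sections disagree on what the monitoring committee sees.

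The documents do not show that bias will occur, who would introduce it, or which arm it would favour. They give no expected event rate, so no size of bias can be derived. What can be said is how sensitive the comparison is: 3.1 percentage points per reclassified participant, assuming the planned 32 per arm and that the participant has no other counted event. This warrants a change of wording. It does not undermine the SPADI comparison.

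**What to change.** 1. In Adverse Reaction Reporting, align the outcome with the outcome table: all adverse events reported after injection are recorded and compared by arm, whatever the attribution.
2. Make any judgement of relatedness a secondary description, made from case summaries with the injector masked, by someone who did not inject.
3. Reconcile Adverse Reaction Reporting with Data Safety monitoring so that the existing committee receives all adverse events. Keep the hospitalisation or antibiotic category only as the trigger for expedited reporting. The count behind the adverse event stopping ground is then defined.

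The cost is a wording amendment, masked summaries for whatever events occur among 64 participants, and a small amount of extra committee time. Clinical care and sample size do not change.

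### Safety sits inside a primary no-worse objective but is elsewhere a secondary outcome with no margin; no adverse-event questions are planned after the clinic visit, and the monitoring committee's remit is stated two ways

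*Protocol*

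**What the plan says.** **Objective.** The protocol's Primary objectives ask whether care "delivered by the physiotherapist is no worse than the same type of care delivered by the orthoapaedic surgeon", and apply this "with respect to safety, access, effectiveness and efficiency".

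**Status of adverse events.** Adverse Reaction Reporting states: "Adverse events attributable to the trial are one of the secondary outcome measures". The Stage 2 outcome table lists the incidence of adverse events without limiting it to attributable ones, and marks SPADI as the Stage 2 primary outcome. The Sample size paragraph gives a margin for SPADI and none for safety.

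**Collection.** The outcome table names the source as the "Adverse event reporting mechanism". Adverse Reaction Reporting explains it: "Participants will be instructed through their post injection information sheets to report any such concerns to the research team". The participant measures at 6 and 12 weeks are SPADI, pain VAS, global rating of change and EQ-5D-5L, with satisfaction added at 12 weeks.

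**Committee.** Adverse Reaction Reporting first sends attributable adverse events to both the ethics committee and the monitoring committee. It then says that an "adverse event reportable to the data safety monitoring committee will be defined as one that requires hospitalization or antibiotic treatment", the antibiotics being for infection. Data Safety monitoring says that "a data/safety monitoring committee will review any adverse events associated with the project". It also lists an excessive prevalence of adverse events as a situation for stopping, with no threshold and without saying who applies the rule.

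**The concern.** Three things do not fit together.

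- A no-worse claim on safety needs a margin and a sample size to match. The protocol gives neither, and elsewhere it places adverse events among the secondary outcomes.
- Events after departure are recorded only if the participant takes the initiative. Incomplete reporting lowers the count in both arms, and two low counts can look like equal safety.
- If the committee receives only hospitalised or antibiotic-treated cases, it cannot judge how prevalent adverse events are overall. If it receives all events, the reporting definition is wrong as written.

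At stake are the safety conclusion and the usefulness of safety monitoring. The SPADI comparison is not affected. A statistical analysis plan could settle how events are analysed, but it cannot supply events that were never asked about.

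**Working it through.** **1. The plan's own sample size.** Inputs from the Sample size paragraph: SD 21.7, margin 15, alpha 0.05, power 80%.

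n per group = 2 × 21.7² × (1.645 + 0.842)² / 15² = 25.9, so 26 by the normal formula. The t-based calculation gives 27, with power 0.806. Both use one-sided 0.05. Allowing for drop-out, 54 / 0.85 = 63.5, so 64 (32 per group). The stated figures reproduce, but they concern SPADI only.

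**2. What no events in one arm would show (n = 32).**

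- One-sided 95% upper limit: 1 − 0.05^(1/32) = 8.9%.
- Two-sided 95% upper limit: 1 − 0.025^(1/32) = 10.9%.
- With 27 per group, the number left after the planned drop-out, the limits are 10.5% and 12.8%.

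**3. Chance that an event never appears in an arm, even with complete reporting.** The protocol gives no event rates, so these are assumed.

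- True rate 1%: 0.99^32 = 72%.
- True rate 2%: 0.98^32 = 52%.

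**4. The comparison between arms.** For 0/32 against 0/32, each limit of the Newcombe interval for the difference is z² / (n + z²).

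- 95%: 3.84 / 35.84 = ±10.7 points.
- 90%: 2.71 / 34.71 = ±7.8 points.
- With one event in each arm, the 95% interval is ±12.9 points.

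**5. Size of a no-worse test on safety.** Assumed: equal true rates p, margin m, one-sided 0.05, 80% power.

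n per arm = 2p(1 − p)(1.645 + 0.842)² / m²

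| True rate | m = 2 points | m = 5 points | m = 10 points |
| --- | --- | --- | --- |
| 1% | 307 | 49 | 13 |
| 2% | 606 | 97 | 25 |
| 5% | 1469 | 235 | 59 |
| 10% | 2783 | 446 | 112 |

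At margins of 5 points or less, 32 per arm is too few at every rate shown. The normal approximation is rough at 1% to 2%, but step 4 agrees with it: no events in either arm leaves 7.8 points inside the 90% interval, so a 5-point excess is not excluded.

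**6. The committee statements side by side.**

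| Place in the protocol | Events that reach the committee |
| --- | --- |
| Adverse Reaction Reporting, earlier sentence | those attributable to the trial |
| Adverse Reaction Reporting, last sentence | those needing hospital admission, or antibiotics for infection |
| Data Safety monitoring | any associated with the project |

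The first and third are broad and the second is narrow. The prevalence-based stopping situation fits only a broad reading.

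**The case against.** Several parts of the opposing case stand.

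- **Collection is not wholly spontaneous.** Participants stay at least 30 minutes, the clinician is to watch for reactions and completes a treatment form, and non-urgent events seen by the supervising surgeon go on an adverse incident form. A reader might infer that every event depends on a volunteered report. The documents do not support that. They do show that no solicited collection is specified, and that after departure self-report is the only stated route. The global rating can record worsening but does not identify an event.
- **The stopping rule is not assigned to the committee.** A reader might infer that the committee lacks the data for its own rule. Data Safety monitoring does not say who applies the rule, and gives interim analyses to the biostatistician.
- **The remit conflict may be loose drafting.** The last sentence of Adverse Reaction Reporting could be a threshold for individual reporting rather than a limit on what the committee sees. That is possible, but the text does not say so.
- **Whether 32 per arm is too few depends on the margin.** A reader might infer that this size cannot support any no-worse statement on safety. At a 10-point margin and true rates of 1% to 2%, the formula asks for only 13 to 25 per arm. That margin is five to ten times the event rate, but the protocol rules no margin in or out.
- **Nothing points to unequal reporting between arms.** Participants are blinded to the clinician's profession, and no arm-specific reporting route is described. The fault is possible under-counting in both arms, not a demonstrated bias towards one.

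Detailed analysis of a secondary safety outcome may also properly sit in a statistical analysis plan. That does not answer the conflicts within the protocol or the absence of solicited collection.

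**Conclusion.** The point holds in two parts.

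Wrong as written: safety is a domain of a primary no-worse objective in one section and a secondary, attribution-limited outcome in another, and the committee's remit is stated both broadly and narrowly. These findings rest on the text alone.

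Open to cheap improvement: no adverse-event questions are specified for the 6- and 12-week follow-up, although forms are already sent then.

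On size, 0/32 in an arm is compatible with a true rate up to 8.9% (one-sided) or 10.9% (two-sided), and 0 against 0 leaves a difference of about 8 to 11 points open. Under assumed rates of 1% to 10%, 32 per arm is too few for a margin of 5 points or less. The rates and margins are assumptions, because the protocol states neither. The change should be made, but the SPADI comparison stands without it.

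**What to change.** 1. Add the same short set of adverse-event questions to the existing 6- and 12-week participant forms in both arms. The Budget section already covers postage for these forms.
2. Reconcile Adverse Reaction Reporting with Data Safety monitoring, so that the events sent to the committee match what it is said to review and the stopping situation listed, and state who applies the stopping rules.
3. Reconcile primary objective 2 with the secondary status of adverse events. Report event rates per arm, and their difference, with exact or score 95% confidence intervals, and draw no no-worse conclusion on safety. State whether the outcome is all adverse events or only those attributable to the trial.

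The cost is a few lines on existing forms, some rewording, slightly more adverse-event processing and a more modest safety claim. The sample size and treatment do not change.

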**Data Safety monitoring**

The biostatistician will monitor the progress of this project through interim statistical analyses, and a data/safety monitoring committee will review any adverse events associated with the project.

Stopping rules will be applied to the following situations:

• Treatments found to be convincingly different

• Treatments found to be convincingly not different

• Adverse events too prevalent

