## Statistical Analysis

All statistical analyses will be performed on an intention to treat basis using the statistical package SPSS (V19.0, IBM, New York, USA), with alpha level set at 0.05.

The analysis of the GEE will be conducted using SAS Statistical Software version 9.2.

**Stage 1:**  Agreements between the decisions from the two clinician assessors will be investigated using the proportion of observed agreement, the probability of chance agreement, and the kappa statistics with the 95% confidence intervals.

**Stage 2:** For continuous outcomes, normality of data will be assessed and parametric tests applied if normality is upheld. Treatments from the two clinicians will be compared over time (pre- to post-intervention) on an intention-to-treat basis using the generalised estimating equation (GEE) approach (Liang and Zeger1986) with an exchangeable working correlation structure to account for within-subject correlation for repeated measurements. With the GEE, a normal distribution with an identity link will be used for continuous outcome measures. The respective pre-condition baseline scores will be included as a covariate. The effects of time (within-group differences), practitioner (between-group differences), and practitioner by time interaction (between-group differences over time) will be included in all models and assessed using the Wald χ2 test. Model fit and assumptions will be checked were appropriate within the GEE framework. The GEE approach works well with missing observations on outcome measures, assuming that they are missing completely at random (MCAR). The validity of this assumption will be examined. If the MCAR assumption was violated, adjustment using weighted GEE (Hogan et al., 2004) will be performed. Appropriate post hoc tests will be conducted if significant main or interaction effects are identified from the omnibus analyses.

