**Sample size:** Assuming α = 0.05, β = 0.2, and a standard deviation of 21.7 points of the change in scores from baseline, we estimate that 54 participants (27 per group) will be required to test for a comparative efficacy between the two treatments with a noninferiority margin of 15 points in the SPADI scores. The above parameter values for the power calculation are based on previous study on comparing the responsiveness for SPADI and several indices in patients receiving corticosteroid injection therapy (Ekeberg et al., 2010), where the minimum clinically important difference (MCID) for the SPADI is 23.1 points at 6 weeks. The calculation is conservative in the sense that it ignores the added power inherent in the repeated measures design. However, it is appropriate when treatment comparisons at the two individual time points (6 weeks and 12 weeks) are performed to assess the interaction treatment effect at different time after the injection. Allowing for a conservative drop-out rate of 15%, we will recruit a total of 64 participants (32 per group) for stage 2. In order to obtain this number, we anticipate needing 128 recruits into stage 1 because we estimate that 50% of stage 1 participants will be eligible to enter stage 2.

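### The protocol commits to stopping on interim treatment comparisons, but sets alpha and sample size for a single look and does not tie its no-difference rule to the 15-point margin

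*Protocol*

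**What the plan says.** In the protocol, the Data Safety monitoring section (under Governance and Safety) makes a firm commitment: "The biostatistician will monitor the progress of this project through interim statistical analyses". It then lists three situations in which stopping rules will be applied. Two compare the arms: "Treatments found to be convincingly different" and "Treatments found to be convincingly not different". The third concerns the frequency of adverse events. In that section the data/safety monitoring committee's stated task is to review adverse events; the interim analyses fall to the biostatistician.

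The Statistical Analysis section covers all analyses "with alpha level set at 0.05". Its sample-size paragraph starts from "Assuming α = 0.05, β = 0.2, and a standard deviation of 21.7 points of the change in scores from baseline" and a "noninferiority margin of 15 points in the SPADI scores", and concludes: "we estimate that 54 participants (27 per group) will be required". Recruitment is then raised to 64 (32 per group) for 15% drop-out. The paragraph calls the calculation conservative only because it ignores the extra power from repeated measures.

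The second primary objective asks whether the physiotherapist's care is no worse than the surgeon's.

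**The concern.** Two things do not fit together.

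First, a trial that may stop on its comparative results has more than one chance to reach a conclusion. To keep the overall error at 0.05, part of the alpha must be set aside for the interim, or the interim threshold must be so strict that it uses almost none. The protocol indicates neither, and its sample size uses the whole 0.05 at the end.

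Second, a finding of no difference does not answer a noninferiority question. Noninferiority is shown when the confidence limit lies inside the 15-point margin. A rule that does not mention the margin could end the trial on data that leave a deficit close to 15 points open. What is at stake is the credibility of the main Stage 2 conclusion.

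**Working it through.** **Inputs from the protocol (sample-size paragraph).** SD of change 21.7; margin 15; alpha 0.05 (sidedness not stated); power 80%; 27 evaluable per group; drop-out 15%. A true difference of 0 is assumed.

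**Step 1: reproduce 27 per group.**
- Normal approximation, one-sided 0.05: n = 2 × [21.7 × (1.645 + 0.842) / 15]² = 25.9, so 26.
- t-test version: noncentrality = 15 / (21.7 × √(2/27)) = 15 / 5.906 = 2.54 on 52 df. Power is 80.6% at 27 per group and 79.2% at 26, so n = 27.
- Drop-out: 54 / 0.85 = 63.5, so 64.
- One-sided 0.025 would need 33 (normal) or 34 (t).

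The stated figure is therefore a fixed design with the whole one-sided 0.05 spent at one final analysis.

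**Step 2: overall type I error if interim looks are added and the final test stays at 0.05.** The number, timing and threshold of looks are assumptions. Looks are equally spaced, with Z at look k equal to the sum of k independent standard normals divided by √k. The overall error is the probability under the null that any look crosses its threshold. For one interim this is 1 − P(Z₁ ≤ c₁, Z₂ ≤ c₂) with correlation √0.5 = 0.707 (two-sided: the same with absolute values). Rows with more looks come from 1,000,000 simulated trials.

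| Looks including final | Interim p<0.05, one-/two-sided | Interim p<0.01, one-/two-sided | Interim p<0.001, one-/two-sided |
|---|---|---|---|
| 2 | 8.0% / 8.3% | 5.4% / 5.5% | 5.0% / 5.0% |
| 3 | 10.1% / 10.7% | 5.7% / 5.9% | 5.0% / 5.1% |
| 4 | 11.7% / 12.6% | 6.0% / 6.2% | 5.1% / 5.1% |
| 5 | 13.0% / 14.2% | 6.3% / 6.5% | 5.1% / 5.1% |

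The one-sided figures apply to a false noninferiority claim, if the no-difference rule is read as early success. The two-sided figures apply to a false claim that the arms differ. If the no-difference rule is a futility stop, it does not raise type I error; it raises type II error, for which the 27 per group makes no allowance.

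**Step 3: what a half-information look can show.** Half of 54 is 27 participants, about 14 per arm.
- SE = 21.7 × √(2/14) = 8.20.
- t(26), 95th percentile = 1.706, so the 90% half-width is 8.20 × 1.706 = 14.0 points.
- The interval is 28 points wide, nearly twice the margin. Its half-width is almost the whole margin.

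At that look, an upper limit inside 15 points requires an observed deficit of no more than 15 − 14.0 = 1.0 point. Failing to see a difference is a much weaker condition.

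**Step 4: cost of a formal early noninferiority stop.** With two looks and overall one-sided 0.05, O'Brien-Fleming boundaries give nominal levels of 0.0089 (interim) and 0.047 (final). The inflation factor is 1.01: 27 × 1.0115 = 27.3, so 28 per group.

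**The case against.** The strongest reply is that nothing here proves inflation. The word convincingly does not naturally mean p<0.05; the blanket 0.05 can be read as the overall level; and the number of looks and the boundaries are often set in a statistical analysis plan or monitoring charter, neither of which is at hand. With an interim threshold of p<0.001 the overall error stays at about 5.0%, so combining an interim look with a full-alpha final test is not in itself an error.

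Most of this stands. A reader might infer that the trial's error rate is 8% or more. The protocol does not support that, because it fixes neither the threshold nor the number of looks. Missing boundaries would not be a finding on their own either.

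A reader might also read the no-difference rule as plain non-significance. On that reading, a half-information look with a true 15-point deficit would trigger a stop 58% of the time. The documents do not support that reading: a non-significant result with 14 per arm is not convincing evidence of anything. Judged against the margin with a 90% interval, a false noninferiority conclusion at that look would occur 5.0% of the time.

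What survives is in the stated text. The protocol says comparative stopping rules will be applied, while its alpha and sample size are those of a single look. One of those rules is worded in terms that do not match the noninferiority question.

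**Conclusion.** The point holds in a limited form. The overall error rate is not controlled by anything the protocol states. How far it departs from 0.05 cannot be determined from the document: from negligible with a strict interim threshold to about 13–14% with five looks each at 0.05. These figures assume equally spaced looks and a final test at full 0.05. The effect falls on type I error if the no-difference rule is an early success claim, and on power if it is a futility stop.

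Separately, and whatever the threshold, the no-difference rule is not expressed against the 15-point margin. The ±14-point interval assumes a look at half information and the protocol's own SD of 21.7. This should be corrected; it does not undermine the design as a whole.

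**What to change.** Change the Data Safety monitoring section in one of these ways.

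1. **Preferred:** remove the two comparative stopping rules and limit interim review to safety by the data/safety monitoring committee, keeping the adverse-event rule. Alpha and sample size need no change. The cost is no early stop for noninferiority and no stated early stop if the physiotherapist arm is clearly less effective.
2. **If a comparative look is to stay:** one look at half information, only for the physiotherapist arm being worse on SPADI, at p<0.001, with no stop for lack of difference. Such a stop cannot produce a noninferiority claim, and the final 0.05 is essentially unchanged. The cost is again no early noninferiority stop.
3. **If an early noninferiority stop is wanted:** define it against the 15-point margin, state the number and timing of looks, use an O'Brien-Fleming boundary, and lower the final nominal level to match (about 0.047 one-sided with two looks). This needs about 28 evaluable per group instead of 27. At 15% drop-out, 28 / 0.85 = 32.9, so 33 per group (66 in total, against 64). The planned 32 per group would be enough only if drop-out stays at or below 4/32 = 12.5%.

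Under options 2 and 3, the Statistical Analysis section should also say that 0.05 is the overall level and state its sidedness.
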